### Economic data

We will calculate QALYs using the EuroQol-5D (EQ-5D)-3 L measure of health-related quality of life [40]. The EQ-5D consists of five dimensions in the domains of mobility, self-care, usual activities, pain/discomfort and anxiety/depression, each scored on three levels (no problems, some problems or extreme problems) and classifies individuals into one of 243 health states. Health states are converted into a single summary index by applying weights to each level in each dimension derived from the valuation of EQ-5D health states in adult general population samples [41]. We will collect participants’ use of BA and CBT from clinical records, with information on additional resources involved (for example, training, preparation, supervision and so forth) collected directly from therapists. We will measure all other health and social care services used, including medication prescription and use, and productivity losses using the Adult Service Use Schedule, designed on the basis of previous evidence of service use in depressed populations [42]. We will also measure productivity losses using the absenteeism and presenteeism questions of the World Health Organization’s Heath and Work Performance Questionnaire [43]. We will calculate intervention costs using a standard micro-costing (bottom-up) approach [44], which will be based on therapist salaries plus employers costs (national insurance and superannuation contributions) plus appropriate capital, administrative and managerial overheads. We will take costs for NHS hospital contacts from NHS reference costs and apply nationally applicable unit costs to all community health and social care contacts [45]. We will take the cost of medications from the British National Formulary [46].

### Process data

In addition to information on age of depression onset and number of previous episodes collected using the SCID [28], we will also collect data on changes in specific behaviour (Behavioural Activation for Depression Scale) [47], changes in beliefs (Dysfunctional Attitude Scale) [48], ruminative response style (Ruminative Response Scale of the Response Styles Questionnaire) [49], hedonic tone (Snaith-Hamilton Pleasure Scale) [50], acceptability of BA and CBT for participants and clinicians (assessed with qualitative process studies), and per-protocol (PP) treatment adherence (from therapist case records). We will collect qualitative data via semi-structured interviews and written responses to access participants’ accounts of the mechanisms and impacts of treatment. At the end of treatment, participants will write short accounts of their experiences of, and perceived impacts of, treatment in response to open-ended questions. Additionally, we will undertake semi-structured interviews designed to obtain a more in-depth understanding of the on-going mechanisms and impact of treatment with purposively sampled participants and therapists building on the analysis of the written accounts. Interviews will focus on the participants’ views of the role of cognitive and behavioural change strategies and broader impacts of treatment in participants’ lives. Integration with the quantitative process data will enhance understanding of change mechanisms that can improve these treatments’ potential efficacy [51,52].

### Sample size calculation

We have estimated the non-inferiority margin for the primary outcome (PHQ 9) using two potential approaches with reference to: (1) the effect size of historical trials comparing BA versus control; and (2) the published minimum clinically important difference for the primary outcome (PHQ-9) of 2.59 to 5.00 [53]. Based on our meta-analysis, BA was superior to control in depression score by a mean of 0.7 SD units (95% CI: 0.39 to 1.00) or 3.8 (2.1 to 5.4) on PHQ-9 score units (assuming an SD of 5.4 from Lowe and colleagues [53]). It has been proposed that non-inferiority margins be taken as ~0.5 × mean control effect size (that is, 0.5 × 3.8 = 1.90) or as the lower 95% limit of the control effect size (that is, 2.1) [54,55]. To ensure the adequacy of this trial to test non-inferiority between BA and CBT, we therefore examined a number of potential scenarios taking in account the potential uncertainty in the non-inferiority margin for the primary outcome (Table 1).

**Table 1 T1:** Sample size calculation

**Approach**	**MICD**	**Power**	**Attrition rate**	**Sample size per group***
50% BA-control effect size	1.90	90%	20%	220
50% BA-control effect size	1.90	80%	20%	160
LCI BA-control effect size	2.10	90%	20%	180
LCI BA-control effect size	2.10	80%	20%	135
Lower MCID	2.59	90%	20%	120
Lower MCID	2.59	80%	20%	90

*Calculated assuming Patient Health Questionnaire 9 SD of 5.4 [33] and 1-sided 2.5% alpha using NQuery v7.0 MTE0-6, NQuery Statistical Solutions, [name]. BA, behavioural activation; LCI, lowest confidence interval; MCID, minimum clinically important difference.

We have selected a conservative non-inferiority margin of 1.90 and power of 90%. As a consequence, we will need to recruit a total of 440 participants to detect a between-group non-inferiority margin of 1.90 in PHQ-9 at 1-sided 2.5% alpha, allowing for 20% attrition caused by drop outs and protocol violators. Furthermore, although previous trials of CBT have shown little or no effects of clustering in outcome by therapists, even when delivering group CBT [56,57], if we were to assume a small therapist clustering effect (that is, intra-cluster correlation coefficient of 0.01) this sample size would still have 80% power for a non-inferiority margin of 1.90 in PHQ-9 at 1-sided 2.5% alpha, allowing for 20% attrition.

Our sample size is inflated by 20% for participant drop out to take account of those that exit the trial and refuse follow-up assessment, although our experience running large primary care trials of depression treatment is that attrition rates will be less than this. Therefore, we intend to recruit 440 participants to the trial, 220 per arm.

### Data analysis

All analyses will be carried out using an *a priori* statistical analysis plan prepared in the first 6 months of the trial and agreed with the Trial Management Group, Trial Steering Committee (TSC) and the Data Monitoring Committee.

Equivalence of baseline characteristics and outcomes in the two groups will be assessed descriptively. Since differences between randomised groups at baseline could have occurred by chance, no formal significance testing will be conducted. We will also undertake a descriptive analysis of the baseline patient characteristics according to the recruitment method (IAPT versus case note review).

We will analyse and report primary and secondary outcomes in accordance with reporting guidelines for non-inferiority and equivalence trials [27]. In a superiority trial, ITT analysis is conventionally used as the most conservative approach to minimise the possibility of a type I error - that is, falsely concluding that one treatment is superior to another. ITT includes data in the primary analysis from participants who drop out or violate the protocol to ensure differences between treatments under test are not falsely inflated and ensuring the most rigorous conditions apply before rejection of the null hypothesis (that is, treatment A is not superior to treatment B). However, in non-equivalence trials the null hypothesis is the opposite, and states that the experimental treatment is inferior to the reference treatment. CONSORT guidelines for such trials [27] recommend analyses to maximise the chances of finding a difference between treatments ensuring stringent conditions apply before rejection of the specific non-inferiority null hypothesis. Paradoxically, because conventional ITT analysis tends to bias towards not finding a difference, adopting an ITT approach could make the null-hypothesis easier to reject in non-inferiority trials by a “blurring of the difference between the treatment groups [which] increases the chance of finding equivalence” [58] - that is, a false non-inferiority result (type I error). Whilst the CONSORT guidelines recommend a PP approach (that is, analysis according to actual treatment received) as the conservative non-inferiority analysis option, given the potential biases of both PP and ITT analyses, we agree with the European Agency for the Evaluation of Medicinal Products that security of inference depends on both PP and ITT analyses demonstrating non-inferiority of the primary outcome [55]. We will, therefore, check for non-inferiority in PP and ITT populations, conducting sensitivity analyses on the primary outcome for PP and imputed ITT populations to check the security of inference of non-inferiority. We will also conduct sensitivity analyses using different definitions of PP adherence. We will include varying proportions of PP participants in these sensitivity analyses populations, depending on how much of each therapy they have received, ranging from 40 to 100% of planned therapy sessions. If non-inferiority is consistently shown by these analyses, we will proceed to assess superiority of CBT versus BA - that is, the CI lower bound lies above 0. If conclusions are inconsistent across analyses we will revert back to primacy of the PP analysis to confirm or refute the non-inferiority hypothesis.

The primary analysis will compare primary and secondary outcomes between BA and CBT groups at 12 months after randomisation adjusting for baseline outcome values and stratification variables (symptom severity, site, antidepressant use) and fitting therapist as a random effects variable. The one-sided 97.5% CI for the between-group difference will be estimated and non-inferiority of BA compared to CBT will be accepted (in a 0.025 level test) if the lower bound of the 97.5% CI lies within the non-inferiority margin of −1.90 in PHQ-9 score. If non-inferiority is shown, we will then test for superiority of CBT over BA (that is, lower bound of the 97.5% CI lies above 0). We will check for non-equivalence at all follow-up points using the same approach. Secondary analyses will be undertaken to compare groups at follow-up across 6, 12, and 18 months using a repeated-measures approach. The analysis will be extended to fit interaction terms to explore possible differences in treatment effect in baseline symptom severity and antidepressant usage. Sensitivity analysis, making different assumptions about the imputation model used, will be conducted for both primary and secondary analyses to assess the likely impact of missing data. Models will be fitted using generalized linear mixed models and undertaken in STATA v.11, STATA, StataCorp LP, [name]. We will also analyse the relative proportions of participants meeting criteria for “recovery” (proportions of participants with PHQ-9 scores ≤9) and “response” (50% reduction in scores from baseline) on the PHQ-9.

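### The plan says non-inferiority rests on both the PP and the ITT analysis, then lets PP alone decide when they disagree, so ITT can never change the conclusion

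*Protocol article*

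**What the plan says.** All of the relevant text is in the Data analysis section of the protocol article.

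- The authors explain why ITT can make false non-inferiority more likely, and note that the reporting guideline they follow treats PP as the conservative choice. They then decline to rely on PP alone. Their reason is "given the potential biases of both PP and ITT analyses", and their position is that "security of inference depends on both PP and ITT analyses demonstrating non-inferiority of the primary outcome".
- They plan further sensitivity analyses with other definitions of PP adherence, "ranging from 40 to 100% of planned therapy sessions".
- They make the superiority step conditional on consistent non-inferiority across the analyses.
- The paragraph closes with the rule for disagreement: "If conclusions are inconsistent across analyses we will revert back to primacy of the PP analysis to confirm or refute the non-inferiority hypothesis".

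The next paragraph gives the acceptance criterion, that non-inferiority is accepted "if the lower bound of the 97.5% CI lies within the non-inferiority margin of −1.90 in PHQ-9 score". It does not say which population that interval comes from, so it does not settle the matter.

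**The concern.** The two statements cannot both govern the non-inferiority conclusion. A requirement that both analyses pass does its work only when they disagree, and the closing sentence hands every disagreement to PP.

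This matters because PP membership depends on how much therapy a patient took up after randomisation. Patients who stay with BA need not be comparable with those who stay with CBT, so the PP contrast is not protected by randomisation. The protocol itself names PP bias as a reason for not relying on PP alone. If that bias favoured BA, the trial could declare BA non-inferior although the randomised comparison had failed to show it. This is the trial's headline conclusion.

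**Working it through.** **Step 1. The decision rule, case by case.**

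| PP | ITT | Rule as written | Both required |
|---|---|---|---|
| pass | pass | accept | accept |
| fail | fail | reject | reject |
| fail | pass | reject | reject |
| pass | fail | **accept** | **reject** |

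The third column always equals the PP result. The rules differ only in the last row, which is also the only row where ITT adds protection beyond PP.

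**Step 2. Inputs.** From the Sample size calculation section: margin 1.90, one-sided alpha 0.025, SD 5.4, 220 per arm, and 20% attrition covering dropouts and protocol violators. Taking off that 20% gives 220 × 0.8 = 176.

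**Step 3. The plan's own figure.** The noncentral-t calculation for margin 1.90, SD 5.4 and 90% power gives 171 per arm, and 171/0.8 = 213.75, so 214. The stated 220 looks like this figure rounded up. The inputs are therefore the plan's own.

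**Step 4. Model.** Differences are signed so that a negative value means BA is worse, matching the −1.90 limit. For n per arm and true difference δ:

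- SE = 5.4 × √(2/n)
- a = (δ + 1.90)/SE − 1.96
- P(pass) = Φ(a)
- P(both pass) = Φ₂(a_ITT, a_PP; r), where r = √(n_PP/n_ITT) because PP is nested in ITT

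Therapist clustering and covariate adjustment are left out.

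Two sets of sizes are used. The first is ITT 220 (imputed) and PP 176. The second is ITT 176 and PP 141, which takes the 20% off twice (176 × 0.8 = 140.8) and is an assumption. The first set gives SE_ITT = 0.515, SE_PP = 0.576 and r = 0.894.

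**Step 5. False non-inferiority, with the true ITT difference at −1.90.** The PP bias towards BA is assumed. For example, at 0.5 points and 176 per arm, a_PP = 0.5/0.576 − 1.96 = −1.09 and Φ(−1.09) = 0.138.

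| Assumed PP bias | As written, 220/176 | Both, 220/176 | As written, 176/141 | Both, 176/141 |
|---|---|---|---|---|
| 0 | 2.5% | 1.5% | 2.5% | 1.5% |
| 0.25 | 6.4% | 2.1% | 5.8% | 2.1% |
| 0.5 | 13.8% | 2.4% | 11.9% | 2.4% |
| 1.0 | 41.2% | 2.5% | 34.3% | 2.5% |
| −0.5 (against BA) | 0.2% | 0.2% | 0.3% | 0.3% |

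**Step 6. The other direction.** Suppose PP sits at the margin and ITT is diluted by an assumed 0.5 points (220/176). ITT alone would then accept in 16.1% of trials, while the rule as written holds 2.5%. Protection against dilution is intact.

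**Step 7. Power at a true difference of zero.**

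| Per arm, ITT/PP | PP alone | Both required | PP passes, ITT fails |
|---|---|---|---|
| 220/176 | 91.0% | 90.4% | 0.6% |
| 176/141 | 84.0% | 82.8% | 1.2% |

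**The case against.** The best defence is that the order is fixed in advance and PP is the analysis the cited guideline regards as conservative. The plan names dilution in ITT as the main route to false non-inferiority, and Step 6 shows that the rule guards fully against it. One could also read the both-analyses sentence as a remark on strength of evidence, with the closing sentence as the actual rule. The first part stands and limits the point to one direction. The second does not resolve the conflict. The authors give PP bias as a reason for wanting both analyses, and fixing a rule in advance does not stop it from cancelling the safeguard stated just before it. Nor is this detail left to the analysis plan, since the fallback is stated here as the decision rule.

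Three stronger readings are tempting, and the document supports none of them.

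- *That the rule inflates the error rate as such.* With an unbiased PP analysis the rate is 2.5%. Inflation needs a bias towards BA. The article gives no size or direction for one, and it describes the same session length, frequency and maximum for both arms.
- *That the 40 to 100% thresholds allow a choice among several tests.* The article calls these sensitivity analyses and nowhere says that any one passing would suffice. The main PP definition may be fixed in the analysis plan, which is not shown.
- *That disagreement would be frequent and the fallback routine.* This needs subset sizes the article does not give. Most disagreement between ITT and one PP set at a true difference of zero would be ITT passing and PP failing (5.4% at 220/176, 8.2% at 176/141), which gives no claim under either rule.

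**Conclusion.** The contradiction is real and rests on the text alone. As written, ITT has no influence on the non-inferiority conclusion, although the plan says that conclusion depends on it. What is lost is one-directional: the check on selection bias in PP when PP passes and ITT fails.

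The size is conditional. Without PP bias, the written rule holds its nominal 2.5%, about 1 percentage point above the rate when both must pass. With an assumed bias towards BA of 0.25 to 1.0 points, it runs from about 6% to 41% (220/176) or 6% to 34% (176/141), while requiring both keeps it at or below 2.5%. These figures assume SD 5.4, a true ITT difference exactly at the margin and no therapist clustering. They illustrate what the missing safeguard is worth and do not predict the trial's error rate.

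**What to change.** Delete the closing fallback sentence and replace it with a rule along these lines: non-inferiority is concluded only if the ITT analysis and the main PP analysis both have the confidence limit inside the 1.90 margin; if they disagree, non-inferiority is not established. Name both populations in the acceptance criterion in the next paragraph. State that the 40 to 100% session-threshold analyses are supportive only, and align the condition for the superiority step with this.

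If the sponsor prefers PP to decide alone, it should instead withdraw the both-required statement, declare PP the sole primary analysis and present ITT as supportive. That also removes the contradiction, but it openly gives up the check on PP selection.

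The first option costs wording and 0.6 percentage points of power at 220/176 per arm (91.0 − 90.4), or 1.2 points at 176/141 (84.0 − 82.8). At 220/176, joint power stays above the planned 90%, so no larger sample is needed on those sizes. The choice should be made before any unblinded analysis.

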### Randomisation, concealment of allocation, and blinding

Participants will be allocated in a 1:1 ratio to either the BA or CBT arms stratified according to their symptom severity on the Patient Health Questionnaire 9 (PHQ-9) [29] (PHQ-9 <19 versus ≥19), antidepressant use (currently using anti-depressants or not) and recruitment site. A computer-based system will allocate the first 20 participants to each arm on a truly random basis. For subsequent participants, allocation will be minimised to maximise the likelihood of balance in stratification variables across the two study arms. Concealment will be ensured by use of an externally administered password-protected trial website and retaining a stochastic element to the minimisation algorithm. The computer-based allocation and website will be setup and maintained by the accredited Peninsula Clinical Trials Unit, independent of the trial. The participant’s details will be sent to the relevant mental health worker to alert them to contact this person and begin treatment.

All research measures will be applied to both groups of participants equally. Researchers will be blind to group allocation, which will occur after baseline assessments. At follow-up, researchers will be instructed to maintain blindness by reminding participants of the confidential nature of their treatment and the need not to discuss this with researchers. We will test blindness by asking researchers to indicate at follow-up which treatment they believe the participants received and analyse any correlation with outcome.

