## Discussion

This trial is designed to test the clinical and economic benefits of BA compared to the current gold standard psychological treatment of depression, CBT. Our non-inferiority design and analytical strategy will determine if BA is substantially inferior to this standard.

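### The follow-on test labelled superiority of CBT carries a criterion that tests superiority of BA, and if the label is what was meant, placing it behind non-inferiority of BA leaves it void at the planning figures

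*Protocol article*

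**What the plan says.** The Data analysis section of the protocol article describes the follow-on step twice.

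- In the discussion of analysis populations: "If non-inferiority is consistently shown by these analyses, we will proceed to assess superiority of CBT versus BA".
- In the description of the primary analysis: "If non-inferiority is shown, we will then test for superiority of CBT over BA".

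Both sentences add the same definition of success, that the lower confidence bound exceeds 0. The second follows directly on the non-inferiority rule, under which BA is accepted as non-inferior if the lower bound of the one-sided 97.5% interval for PHQ-9 clears −1.90. The section does not state which arm is subtracted from which. It gives no superiority test for the case where non-inferiority is not shown; inconsistent results only send the reader back to the per-protocol analysis of non-inferiority.

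**The concern.** A superiority test placed after a non-inferiority test is sound when both concern the same treatment. Superiority of BA implies non-inferiority of BA, so the second hypothesis is nested in the first. The protocol names the other treatment in the second step, and this raises two problems.

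First, the name does not fit the criterion. Higher PHQ-9 scores are worse. A rule that accepts BA when the lower bound is above −1.90 makes sense only if negative differences mean that BA is worse, as with CBT minus BA. On that scale a lower bound above 0 shows BA better than CBT, not the reverse. With BA minus CBT, the criterion would fit CBT superiority, but a lower bound of −1.90 would then be on the wrong side for non-inferiority of BA. No single sign convention makes both rules right.

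Second, if the name is what was meant and only the bound is corrected, the test has to be passed by data that have already shown BA non-inferior. The result must be significantly against BA and also significantly short of the margin. At stake is whether the pre-specified sequence can reach a formal conclusion in favour of CBT.

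**Working it through.** **Inputs**, from Sample size calculation unless noted:

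- Margin and power: "We have selected a conservative non-inferiority margin of 1.90 and power of 90" per cent.
- SD and alpha: "Patient Health Questionnaire 9 SD of 5.4 [33] and 1-sided 2.5% alpha".
- Attrition: "allowing for 20% attrition caused by drop outs and protocol violators".
- Size: "we intend to recruit 440 participants to the trial, 220 per arm". Analysed per arm: 220 × 0.8 = 176.
- Allocation 1:1 (Randomisation section).
- True difference used for planning: not stated; 0 reproduces Table 1.

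**The plan's own figure.** With margin 1.90, SD 5.4, 90% power and one-sided 2.5% alpha, the t-based calculation gives 171 per arm, and 171 / 0.8 = 214, which rounds up to the stated 220. The other five rows of Table 1 reproduce in the same way. Power with 176 analysed per arm is 91.0%. The inputs are therefore read as the protocol uses them.

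**Condition for passing both steps under the label.** Let D be CBT minus BA in PHQ-9, so that positive values favour BA, with 95% limits L and U.

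- BA non-inferior: L > −1.90.
- CBT superior: U < 0.

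Both together require U − L < 1.90, that is 2 × 1.96 × SE < 1.90, or SE < 0.485.

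**Unadjusted, SE = 5.4 × √(2/n):**

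| Analysed per arm | SE | Interval width | CBT superior if observed CBT advantage exceeds | BA non-inferior if it is below |
|---|---|---|---|---|
| 176 | 0.576 | 2.26 | 1.128 | 0.772 |
| 220 | 0.515 | 2.02 | 1.009 | 0.891 |

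In both rows the two requirements exclude each other, so the joint probability is 0 at every true difference. A width below 1.90 needs about 249 analysed per arm: 2 × (5.4 × 3.92 / 1.90)² = 248.2.

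**Adjusted.** The primary model includes baseline PHQ-9 and the stratification variables, but the document gives no correlation r. Taking SE × √(1 − r²), the interval fits only if r exceeds about 0.54 with 176 per arm, or about 0.34 with 220. The joint probability is highest at a true CBT advantage of 0.95, the middle of the window. The values of r are assumptions.

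| Analysed per arm | r | Width | Best joint probability | Ungated CBT power at the same difference (0.95) |
|---|---|---|---|---|
| 176 | 0.5 | 1.95 | 0 | 48% |
| 176 | 0.6 | 1.81 | 8% | 54% |
| 220 | 0.5 | 1.75 | 14% | 57% |
| 220 | 0.6 | 1.62 | 27% | 64% |

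One limit does not depend on r. At a true CBT advantage of 1.90 the non-inferiority test passes with probability 2.5% by construction, so the gated test cannot succeed more often than that, however precise the trial.

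**Without the gate**, 176 per arm, SD 5.4, power = Φ(d / 0.576 − 1.96): 38% at a true CBT advantage d of 0.95, 74% at 1.5, 91% at 1.90 and 99% at 2.5.

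**If the criterion is what was meant**, the step tests BA over CBT. It is nested and attainable, with 91% power if BA is truly better by 1.90. The label is then the error.

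**The case against.** The strongest reply is that CBT is a slip for BA in both sentences. The stated bound is the standard nested test of the new treatment, and on that reading the sequence is correct. This stands as a possible reading and is why the contradiction comes first here. It does not remove the need for a correction, because the same label appears in both places and a reader cannot tell which half to trust.

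A second reply is that the primary analysis is adjusted and the protocol expects attrition below 20%, so an interval from an unadjusted SD with 176 per arm is pessimistic. That is fair. A zero probability is exact only at the planning SD; with useful covariates and nearly complete follow-up a small window opens. Against this, a therapist effect would widen the interval, and the first of the two sentences demands consistent non-inferiority across several analyses, which is stricter than the single interval used above.

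A third reply is that CBT superiority is not among the objectives, and that the estimate and the repeated-measures comparisons at 6, 12 and 18 months will be reported in any case. This limits the consequence to the formal decision sequence.

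Two stronger readings are tempting and are not supported. A reader might infer that non-inferiority fails whenever CBT is better. It does not: at SE 0.576 it passes about 68% of the time at a true CBT advantage of 0.5 and 38% at 0.95. A reader might also set the gate against the Discussion's statement, "Our non-inferiority design and analytical strategy will determine if BA is substantially inferior to this standard". A CBT test against 0 would not settle that statement, since substantial inferiority would need the whole interval beyond the margin.

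**Conclusion.** The follow-on rule is wrong as written under either reading. On the scale set by the −1.90 rule, its label names CBT and its criterion tests BA. If the criterion is right, the label must change, and the plan then contains no formal test of CBT superiority on the primary outcome. If the label is right, the bound must change and the step then has no function at the planning figures: its probability of success is 0 with 176 or 220 per arm at SD 5.4. Under assumed correlations of 0.5 to 0.6 it is at best between 0 and 27%, and never above 2.5% at a true CBT advantage of 1.90. The ungated test on the same data would have about 91% power there at 176 per arm.

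The point is of moderate weight. The sample size and the primary non-inferiority decision do not depend on the order of these tests. What it changes is which superiority conclusions the pre-specified sequence can reach.

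**What to change.** In both places in the Data analysis section, state the sign of the difference (for example CBT minus BA in PHQ-9, positive favouring BA), report the two-sided 95% interval so that both one-sided 97.5% bounds are available, and replace the follow-on step with wording such as:

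> If non-inferiority of BA is shown, superiority of BA over CBT is tested (lower bound above 0). Whether or not non-inferiority is shown, superiority of CBT over BA is assessed from the upper bound of the two-sided 95% CI (upper bound below 0). The ITT population is the primary analysis for either superiority claim.

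Naming ITT for superiority agrees with the section's own account of why ITT is the conservative choice in a superiority comparison, and settles which result governs if the populations disagree.

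No alpha adjustment is needed. The BA superiority test is nested in the non-inferiority test. BA cannot be both worse by at least 1.90 and not worse at all, so the non-inferiority null and the CBT superiority null are never true together. The two superiority tests together are the ordinary two-sided 5% test.

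The cost is two sentences of wording, with no further participants, data or alpha.
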